## Abstract

**Introduction:** Vulnerably housed individuals, especially those experiencing homelessness, have higher acute care use compared with the general population. Despite available primary care and social services, many face significant challenges accessing needed services. Connect 2 Care (C2C) is a novel transitional case management program that includes registered nurses and health navigators with complementary expertise in chronic disease management, mental health and addictions, social programs, community health, and housing, financial, transportation and legal resources. C2C bridges acute care and community services to improve care coordination.

**Methods and Analysis:** We will perform a mixed-methods evaluation of the C2C program according to the Donabedian framework of *structure, process and outcome*, to understand how program structure and process, coupled with contextual factors, influence outcomes in a novel intervention. Eligible patients are homeless or unstably housed adults with complex health conditions and high acute care use. Change in emergency department visit rate 12-months after program enrolment is the primary outcome. Secondary outcomes include 12-month post-enrolment hospital admissions, cumulative hospital days, health-related quality of life, housing status, primary care attachment and substance use. Qualitative methods will explore experiences with the C2C program from multiple perspectives and an economic evaluation will assess cost-effectiveness.

**Discussion:** Academic researchers partnered with community service providers to evaluate a novel transitional case management intervention for vulnerably housed patients with high acute-care use. The study uses mixed-methods to evaluate the Connect 2 Care program according to the Donabedian framework of structure, process and outcome, including an assessment of contextual factors that influence program success. Insights gained through this comprehensive evaluation will help refine the C2C program and inform decisions about sustainability and transferability to other settings in Canada.

## Introduction

Individuals who experience housing instability are disadvantaged due to poverty and stressors such as isolation, lack of social support, and cultural or racial exclusion (1). These individuals have high morbidity and acute care use compared with the general population (2–5). Among the homeless and vulnerably housed, the probability of survival to age 75 is 32% for men and 60% for women (6). Patients who are homeless remain hospitalized longer, resulting in higher costs, especially when there is concomitant mental illness and addictions (7–11). Homelessness and poverty are significant barriers to care; often forcing individuals to prioritize food and basic needs over adherence to recommended medical care (10, 12, 13). Further, stigma and discrimination in the healthcare system can cause distrust, thus preventing collaborative engagement and leading to acute care presentation after illness severity escalates (14–16).

While primary care and social services are available, they are difficult to access and do not meet the needs of many individuals with housing instability in the community (2, 4, 12, 13). Those discharged into the community are two to four times more likely than the general population to have a repeat emergency department (ED) visit within seven days (4). Some individuals may be attached to a medical home; however, poor continuity among acute care, primary care, and social support services, impedes coordination of care and services (10, 13, 17).

Transitional case management programs can improve health and social outcomes, increase patient and staff satisfaction, and reduce acute care use (18–24). While nurse case managers provide professional multidisciplinary care coordination, community-based programs that include health (or patient) navigators (HNs) can improve access and appropriateness of care (25–30). HNs form supportive relationships with patients and serve as intermediaries between healthcare, social services and the community (29). Previous studies support the effectiveness of HNs in improving care and decreasing acute care use in complex patients; however, individual study results vary, likely due to contextual differences that may be especially important in vulnerable subpopulations (20, 23, 31, 32).

We partnered with an established urban community health center [Calgary Urban Project Society (CUPS)], a non-profit emergency shelter and housing agency (Calgary Alpha House Society), the provincial health system [Alberta Health Services (AHS)], and a provincial grant funding agency (Alberta Innovates), to develop, implement, refine and evaluate a novel transitional case management program that combines elements of intensive case management and health navigation for vulnerably housed and homeless individuals. The Connect 2 Care (C2C) program aims to improve the quality, access and coordination of care for patients with unstable housing and high acute care use. The proposed mixed-methods evaluation will provide a rigorous scientific evaluation of the C2C program.

## Methods and Analysis

### Study Setting

Calgary, Alberta, the fourth largest city in Canada, experienced significant changes leading up to and during the implementation of Connect 2 Care (33, 34). Calgary's population grew by 25% to 1,596,248 over the preceding decade (33). Following exponential growth in homelessness between 1992 and 2008 (34), Calgary's homeless population remained stable and in 2016, when we began this work, the point prevalence of homeless individuals in Calgary was estimated at 3,430 (35). At the time, the rental vacancy rate in Calgary was 7.0% and the average and median market rents were $1,150 CAD/month and $1,120 CAD/month, respectively (36). Additionally, Calgary and Alberta are facing an ongoing opioid overdose epidemic; Alberta has the second highest incidence of opioid poisonings in Canada, with substantial increases in associated ED visits and hospital admissions (37).

### The Connect 2 Care Intervention

C2C is a multidisciplinary mobile outreach team that provides transitional case management, advocacy, and care navigation for socially vulnerable patients. Clinical and operational leadership at CUPS developed the C2C pilot, launched with two registered nurses (RNs) in November 2015, in partnership with Foothills Medical Center, the largest of four tertiary care hospitals in Calgary. With innovation grant funding, we expanded the program across three implementation phases (see Figure 1). In Phase 1 (January–December 2017) two HNs were added; in Phase 2 (January–December 2018) the referral base expanded to all four Calgary hospitals, as well as community agencies, using two additional HNs; in Phase 3 (January–December 2019), the program reached maturity with 2 RNs and 4 HNs. HNs are hired from a pool of emergency shelter outreach workers at Calgary Alpha House Society, a housing, shelter, outreach, and detoxification facility. HNs are acquainted with the target population's social and community context and are provided health and health system navigation training. Collectively, the C2C team has expertise in chronic disease management, mental health, harm reduction and addictions, as well as extensive knowledge of social programs, community health, housing, financial and transportation resources.

**Figure 1 F1:**
[figure not shown]
Program implementation and study timeline.

To be eligible for the program, patients must be ≥ 18 years of age, homeless or unstably housed (38), have ≥ 3 ED presentations, or ≥ 2 hospitalizations within the past year. While definitions of high acute care use vary, we chose the most conservative definition (18) in order to make the program inclusive and allow refinement to occur over the initial phases of implementation. Preliminary data gathered for the first 127 patients referred to the program before expansion indicates that, on average, C2C patients had 9 ED visits in the year prior to referral and 20% had a hospital admission. The most common reasons for admission were cellulitis, sepsis, pneumonia, substance use and other mental health diagnoses. C2C patients were more likely to be male (66%), 29% identified as Indigenous, 88% used substances and 78% were homeless. Referrals are accepted from acute care facilities, health clinics, and community agencies. Reasons for referral include attachment to primary care, housing support, connection to substance use treatment, advocacy, and discharge planning.

C2C works closely with patients to identify their immediate needs, remove barriers to care, and coordinate the *right care at the right time*. C2C patients are assigned to either an RN or HN for case management, depending on medical complexity. The assigned navigator provides intensive case management to the patient for the duration of C2C engagement (with the goal of graduation to other programs within 6 months). The navigator meets with the patient in person to build trust and rapport, complete an intake, develop a care plan, and articulate and set longer term goals. C2C navigators regularly connect with the patient to provide on-going coaching and support to navigate day-to-day crises and challenges while building patient capacity for independence. C2C supports may include connecting patients to long-term community based primary care, providing transportation, accompaniment to appointments, advocating, coaching patients to navigate health, housing, and justice systems, providing health information, and coordinating other needed services. The outreach and mobile capabilities of C2C allow the team to support patients in community, travel between acute care sites and social service agencies, and transport and accompany patients to appointments. Figure 2 depicts the C2C logic model with further details regarding specific activities.

**Figure 2 F2:**
[figure not shown]
Connect 2 Care Logic Model.

### Evaluation Objectives

We aim to understand how structure and process, coupled with contextual factors, lead to program outcomes in a novel transitional case management intervention.

Our study objectives are:

To document the structure and process of the C2C program throughout three implementation phases.To determine the effectiveness of the C2C program, in light of contextual factors, in reducing acute health care use and improving patient-reported outcomes.To explore patient, staff, and program partner experience with the C2C program.To ascertain the cost-effectiveness of the C2C program for the publicly funded health care system.

### Study Design and Evaluation Framework

We have conceptualized our evaluation using a widely accepted paradigm for measuring quality of medical care – Donabedian's model of *structure, process* and *outcome* (39). *Structure* is the setting in which care is provided and includes available resources and organizational inputs. *Process* is the means of providing and receiving care in the health system. *Outcome* is the impact of the care provided, such as the health of users within the system. The Donabedian model provides an evaluative framework based on the construct that the right organizational *structure* leads to improved *processes*, which together lead to better *outcomes* (39). Guided by the United Kingdom Medical Research Council framework for evaluating complex interventions, we extend our evaluation to also include an assessment of contextual factors that influence program success (39, 40). The current C2C program model is depicted in Figure 3.

**Figure 3 F3:**
[figure not shown]
Connect 2 Care Preliminary Program Model.

### Structure and Process

We will document and describe the structure of C2C, as well as its processes and associated metrics. Structural elements include organizational supports, community partners, personnel, and IT infrastructure. Processes include team activities and operational procedures (e.g., program referrals and triage). Process metrics include referral numbers, engagement (i.e., patients who agree to work with C2C staff), enrolment status (i.e., active, graduated, lost to follow up, or deceased), housing stability, primary care attachment, and medication insurance acquisition. We will derive data primarily from meeting notes, program documentation, and team activity logs. To elicit further detail on structure and process, we will supplement with data from qualitative interviews and observations (see below).

### Measures of Effectiveness

#### Acute Care Use

We will use administrative health data to assess acute care use among C2C patients 12-months before and after enrolment: ED visits (primary outcome); hospital admissions; repeat ED visits within 72 h of discharge; unplanned readmissions within 30 days among hospitalized patients; total hospital bed days; deaths; ED and hospital discharge diagnoses; and ICU admissions. Data will be obtained by linking unique provincial health insurance numbers to administrative health data housed by Alberta Health Services.

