#### Within-Subject Comparison

In a within-subject comparison, patients serve as their own controls, eliminating the need to account for confounding due to immutable patient factors. However, observed changes in use may be due to other factors such as changes in health status over time or concomitant interventions. We will use generalized linear mixed-effects models with a negative binomial distribution to examine the ED visit rate, hospitalization rate, 30-day readmission rate and cumulative hospital bed days over the two time periods (12 months before and after enrolment), adjusting for age, sex, ethnicity, and comorbidities. We will use one-way repeated measures ANOVA to assess changes in patient-reported outcomes. We will perform stratified analyses based on phase at time of enrolment and by pre-program ED visit rate.

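### Cutting the within-subject comparison at enrolment counts the acute visit that prompted referral only in the before year, which inflates the apparent fall in ED visits for patients referred from acute care

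*Protocol article*

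**What the plan says.** The Abstract of the protocol article names the primary outcome: "Change in emergency department visit rate 12-months after program enrolment is the primary outcome". The Acute Care Use section sets the windows: "We will use administrative health data to assess acute care use among C2C patients 12-months before and after enrolment". The Within-Subject Comparison section fits negative binomial mixed models "over the two time periods (12 months before and after enrolment), adjusting for age, sex, ethnicity, and comorbidities". The Cost Effectiveness section takes patient-level costs over the same two years around enrolment. Enrolment is therefore the stated cut-point for ED visits, admissions, bed days and cost.

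On how patients reach the program, the eligibility paragraph after the Figure 1 caption says: "Referrals are accepted from acute care facilities, health clinics, and community agencies". It continues: "Reasons for referral include attachment to primary care, housing support, connection to substance use treatment, advocacy, and discharge planning". The Connect 2 Care Intervention section says the pilot began with two nurses in partnership with one tertiary hospital, and that in Phase 2 "the referral base expanded to all four Calgary hospitals, as well as community agencies". The article gives no breakdown by referral source and no interval from referral to enrolment.

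**The concern.** In a before-after comparison the cut-point should not itself be set by the outcome. When an ED visit leads to referral and referral leads to enrolment, the date of enrolment depends on a visit having just happened. The before year then contains that visit by construction, while the after year contains visits only as they arise. The patient need not be enrolled at the bedside: if enrolment follows days later, the prompting visit still lies in the before year.

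The primary outcome would show a reduction even if the program did nothing. The admission count is affected in the same way when an admission prompted the referral. Discharge planning as a referral reason points to some stays being in progress at referral. If enrolment also occurs before discharge, one stay straddles the cut, and its bed days and cost fall on whichever side the counting rule puts them.

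The limitations in the Within-Subject Comparison and Discussion sections cover changes in health, concomitant interventions and other confounding. They do not cover this artefact.

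**Working it through.** **Inputs from the Power Calculation section.** Before rate 9.3 visits/year (Phase 1 patients), after rate 6.5, common SD 10, correlation 0.05, N = 257, 5% significance (two-sided assumed), stated power above 90%.

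**Input not in the documents.** f, the share of patients whose referral from acute care was prompted by an ED visit. It is an assumption, shown over a range.

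**Step 1: reproduce the plan's figure.**
- Planned difference: 9.3 − 6.5 = 2.8 visits.
- SD of the paired difference: 10 × √(2 × (1 − 0.05)) = 13.78.
- Normal approximation: power 90.3%, with 255 patients needed for 90%.
- Paired t: power 90.05%, with 257 patients needed for 90%.

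The stated power reproduces.

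**Step 2: size of the artefact.** Let visits occur at a constant rate λ per year with no program effect. A year chosen because it contains a triggering visit holds λ + 1 visits in expectation; the following year holds λ. Averaged over the cohort, the spurious fall is f × 1 = f visits per patient. As a share of the before rate it is f/9.3; as a share of the planned difference it is f/2.8.

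**Step 3: consequences in the plan's own power framework.** SD, correlation and N are held fixed. The rejection rate with no true effect uses a mean difference of f. The last two columns assume that the 9.3 figure includes the triggering visits and that the after rate stays at 6.5, so the remaining difference is 2.8 − f. Rejection rates and power are from the paired t calculation.

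| f (assumed) | Spurious fall, visits | % of 9.3 | % of 2.8 | Rejection rate, no true effect | Difference left | Power left |
|---|---|---|---|---|---|---|
| 0.25 | 0.25 | 2.7 | 8.9 | 6.0% | 2.55 | 84.0% |
| 0.5 | 0.50 | 5.4 | 17.9 | 8.9% | 2.30 | 76.0% |
| 0.75 | 0.75 | 8.1 | 26.8 | 14.0% | 2.05 | 66.1% |
| 1 | 1.00 | 10.8 | 35.7 | 21.2% | 1.80 | 55.0% |

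The row f = 1 is an upper limit, not an estimate.

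**Step 4: a stay in progress at enrolment.** The article does not say how such a stay is counted. The three usual conventions give different results:
- Split by calendar day: the remaining days fall after enrolment, against the program.
- Whole stay assigned by admission date: all days fall before, in favour of the program.
- Whole stay assigned by discharge date: all days fall after, against the program.

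Hospital cost follows the same pattern. The documents give neither the share enrolled as inpatients nor the days remaining, so no size can be attached.

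**The case against.** **Not every patient has a triggering visit.** A reader might infer that patients are always enrolled during an ED visit or admission. The documents do not support that. Health clinics and community agencies also refer, and Structure and Process treats referral and agreement to take part as separate: "Process metrics include referral numbers, engagement (i.e., patients who agree to work with C2C staff), enrolment status". This stands. It limits the size through f, but does not remove the bias for patients who are referred from acute care.

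**Spanning stays are a data-handling detail.** An article can leave their allocation to the analysis plan. This stands for bed days: it would be wrong to claim that the article's rule pushes the rest of the stay into the after year, because it states no such rule. The ED-visit artefact is different, because it follows from the cut-point that the article does fix.

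**Readmissions.** A reader might infer that 72-hour returns and 30-day readmissions are distorted too. That cannot be determined: the rule for the index discharge is not given, and counting a return after enrolment as a post-enrolment event is reasonable.

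**Overlap with selection on high use.** Eligibility requires high use in the past year, which brings its own regression to the mean, and the triggering visit may be one of the qualifying visits. The two overlap on ED visits. Removing the triggering visit does not cure the selection effect, and the figures above do not include it.

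**Other analyses exist.** The population-level trend is not cut at individual enrolment. That helps interpretation, but the power calculation rests on the within-subject contrast.

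**Excluding the index episode has a price.** The program may shorten the current stay through discharge planning, and starting follow-up at discharge could miss early deaths. Both points stand and shape the fix.

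**Conclusion.** The point holds for patients referred from acute care. Following the stated cut at enrolment inflates the before-to-after fall in ED visits by about f visits per patient, in the program's favour: 9%, 18% or 36% of the planned 2.8-visit difference at f = 0.25, 0.5 or 1. This rests on a constant underlying visit rate, one triggering visit per affected patient, and an f that the documents do not supply. Given the mixed referral sources, the top of that range should not be read as likely.

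For bed days and cost the conclusion is weaker: a stay in progress at enrolment can distort the contrast, in a direction that depends on an unstated rule and by an amount that cannot be computed here. Nothing is concluded about readmissions. The matter is worth correcting because it bears on the primary outcome and is cheap to correct; it does not invalidate the evaluation.

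**What to change.** Amend Acute Care Use, Within-Subject Comparison and Cost Effectiveness as follows.

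1. For patients referred from acute care, define the index episode as the ED visit and/or admission that prompted referral.
2. In the main within-subject analysis, exclude that ED visit and admission from both periods, and end the before year on the day before the index episode starts. Other referrals keep the enrolment date as the cut.
3. Report the bed days and cost of the index stay as a separate category, counted in neither period.
4. Keep counting deaths from enrolment, so that none are lost between enrolment and discharge.
5. Report the plain enrolment-date cut as a sensitivity analysis, so that any discharge-planning effect on the index stay remains visible.
6. Report the share of patients with an index episode, so that readers can see f.

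The cost is one date rule in the linkage program and the matching wording. The before rate will be slightly lower and the apparent reduction less favourable; if f is large, power for the remaining difference should be rechecked.

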#### Patient-Report Outcomes

We will collect the following patient-reported data from C2C patients at 6 and 12 months post-enrolment using in-person structured interviews comprised of closed-ended questions: health-related quality of life using the EuroQoL 5 Dimensions (EQ-5D) questionnaire (41); housing information [where they slept at night for the past 2 weeks and self-perceived stability and satisfaction (42)], primary care data (attachment [yes/no], self-perceived quality) and risk factors {drug intake [DUDIT (43)], smoking (daily/occasional/not at all), and alcohol intake [AUDIT-C (44)]}. We will also ask patients if they have achieved goals that were set at program intake and how the C2C team helped. We will obtain baseline data, including demographic characteristics, housing and income status, substance use, and patient goals from program records. In a subset of participants, we will perform a more detailed housing assessment using the Residential Time-Line Follow-Back method, to determine the number of days in a particular housing type and the number of housing transitions (38). Given the variation and complexity of the study population, we expect loss to follow-up and difficulties in collecting 6 and 12 month post-enrolment data from all engaged patients. The C2C team will utilize their strong relationships with patients and robust partnerships with community agencies and social services to retain engaged patients and locate patients for post-enrolment evaluations. In addition, C2C patients will be provided a $25 CAD VISA gift card at each instance of data collection, to compensate them for their time.

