#### Comparison Cohort

We will identify a contemporaneous comparison cohort using administrative health data for a population not enrolled in the C2C program and who have an ED visit or hospital admission with an associated ICD-10 Z59x diagnosis (problems related to housing and economic circumstances) and at least one visit to a Calgary facility between 2014 and 2019. We will use propensity score matching to create a control group from this population. Propensity scores will be calculated for both the C2C and control cohorts and controls will be matched to C2C enrolled clients. This allows us to account for the covariates that may predict C2C enrolment, approximating random assignment and reducing selection bias between the groups. We will use a generalized linear modeling framework to estimate the effect of C2C enrolment on acute care utilization and death rates between these two groups.

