### Cost Effectiveness

We will perform a cost-utility analysis with a 1-year time horizon, from the perspective of the publicly funded health care system, comparing the C2C program to usual care. The analysis will follow guidance from the Canadian Agencies for Drugs and Technologies (CADTH) (56). Direct patient level health care costs will be obtained from Alberta Health Services (12 months prior to and following program enrolment): hospital admissions, ED visits, urgent care visits, ambulatory care, substance use treatment programs, medication and physician costs. Hospital costs are based on facility-specific costs per day and include direct and indirect costs such as diagnostic imaging, laboratory, housekeeping, administration, etc. Monthly total health care costs will be calculated per patient by summing across available cost data. Program costs will be obtained from the operational budget: wages, training, transportation, management, and IT costs. Health outcomes of interest will be lives lost and the change in health-related quality of life (measured by the EQ-5D). Utility will be derived from EQ-5D data using Canadian based preferences (57). A linear extrapolation of utilities over time will be used to calculate per patient quality-adjusted life years (QALYs).

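### EQ-5D is scheduled only at 6 and 12 months and only in C2C patients, so change from enrolment and the incremental QALY against usual care would rest on assumed utilities

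*Protocol article*

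**What the plan says.** All references are to the protocol article.

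- **Patient-Report Outcomes, timing:** "We will collect the following patient-reported data from C2C patients at 6 and 12 months post-enrolment". The set covers EQ-5D, housing items, primary care items, DUDIT, smoking and AUDIT-C.
- **Patient-Report Outcomes, baseline:** "We will obtain baseline data, including demographic characteristics, housing and income status, substance use, and patient goals from program records". EQ-5D is not in this list, and no research interview at enrolment is described.
- **The Connect 2 Care Intervention:** engagement is planned "with the goal of graduation to other programs within 6 months".
- **Within-Subject Comparison:** "We will use one-way repeated measures ANOVA to assess changes in patient-reported outcomes".
- **Comparison Cohort:** "We will identify a contemporaneous comparison cohort using administrative health data for a population not enrolled in the C2C program". Its stated outcomes are acute care use and death.
- **Cost Effectiveness:** a one-year cost-utility analysis of C2C against usual care. "Health outcomes of interest will be lives lost and the change in health-related quality of life (measured by the EQ-5D"). "A linear extrapolation of utilities over time will be used to calculate per patient quality-adjusted life years (QALYs").
- **Cost-Effectiveness (subsection):** costs and QALYs are to be estimated jointly by seemingly unrelated regression, giving an incremental cost-effectiveness ratio and acceptability curves.

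**The concern.** Health-related quality of life is a named secondary outcome and cost-effectiveness is the last of the study's four objectives. Both need a utility at enrolment, and the second also needs a utility for people who did not receive the program. The stated data collection supplies neither.

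The first EQ-5D falls at the point by which the program hopes to have handed the patient on. Most of any effect during engagement would already be inside the 6-month value. A 6-to-12-month change could be flat or negative after a real early gain, or positive for reasons unrelated to the program.

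In the economic analysis, costs have a counterfactual (the 12 months before enrolment) and QALYs have none. A ratio reported to decision makers would then have a denominator fixed largely by assumption. Acceptability curves would show sampling uncertainty around that assumption and would not show the uncertainty in the assumption itself.

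**Working it through.** **The plan's own figure.** The article gives no sample size, power or utility value for EQ-5D or QALYs, so there is nothing to reproduce on this point. Its only power figure concerns emergency department visits. The SD of the difference is 10 × √(2 × (1 − 0.05)) = 13.78. Then 2.8 × √257 / 13.78 − 1.96 = 1.30, a power of about 90.3% by the normal approximation (90.05% by noncentral t), two-sided 5% assumed. It reproduces and is not touched by this point.

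**What the schedule identifies.** Write U0, U6 and U12 for utility at enrolment, 6 and 12 months.

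| Quantity promised | Needs | Scheduled |
|---|---|---|
| Change in EQ-5D from enrolment | U0 with U6 or U12 | U6, U12 |
| One-year QALY under C2C | U0, U6, U12 | U6, U12 |
| One-year QALY under usual care | utilities without C2C | none |

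Only U12 − U6 is identified. With two occasions, one-way repeated measures ANOVA is equivalent to a paired t-test of that difference.

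**Weight of the missing enrolment value.** With straight lines between time points:

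QALY(C2C) = 0.25·U0 + 0.5·U6 + 0.25·U12

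If usual care is represented by U0 held for one year, its QALY is U0, and

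gain = 0.5·U6 + 0.25·U12 − 0.75·U0.

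A 0.10 shift in U0 moves the gain by 0.75 × 0.10 = 0.075 QALY.

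**Illustration.** All utilities below are assumed.

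U6 = 0.60, U12 = 0.65, so gain = 0.4625 − 0.75·U0:

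| U0 | Gain |
|---|---|
| 0.40 | +0.1625 |
| 0.50 | +0.0875 |
| 0.60 | +0.0125 |
| 0.70 | −0.0625 |

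U6 = U12 = 0.65, so gain = 0.4875 − 0.75·U0:

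| U0 | Gain |
|---|---|
| 0.55 | +0.075 |
| 0.65 | 0 |
| 0.70 | −0.0375 |

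**If the 6-to-12-month line were run back to month 0.** In the first case U0 = 0.60 − (0.65 − 0.60) = 0.55 and the gain is 0.4625 − 0.4125 = +0.05. In the second case U0 = 0.65 and the gain is 0. In both, the result follows from the straight-line assumption and not from data on months 0 to 6.

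**Weight of the missing usual-care value.** Suppose U0 were measured. Usual care over one year still contributes its mean utility × 1 year, so each 0.10 of error in that mean moves the gain by 0.10 QALY. A measured baseline removes the first gap and leaves this one.

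**The other interview measures.** Program records hold a baseline for housing status and substance use, so a crude change from enrolment is possible for these. No baseline is stated for DUDIT, AUDIT-C, the two-week sleeping-place item, smoking or perceived quality of primary care, so change on those instruments is again limited to 6 to 12 months. Primary care attachment also appears as a process metric under Structure and Process, without a time point.

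**The case against.** The strongest reply is that the article is condensed. Its baseline list is introduced as examples, the content of the navigator's in-person intake is not given, and repeated measures ANOVA is more natural with three occasions than with two. A baseline EQ-5D might therefore exist unstated. That possibility stands and limits how firmly its absence can be asserted. It does not settle the point: nothing in the text says such a measurement is made, and even if it were, usual care would still have no utility.

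A reader might go further than the document allows in four ways.

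- *That no patient-reported outcome has a baseline.* Not so: housing status and substance use come from program records, and attainment of the goals set at intake is asked at follow-up.
- *That collecting data only from C2C patients prevents a change from enrolment.* A within-patient change needs a baseline and no comparator. The missing comparator affects only the incremental QALY.
- *That the plan commits to extrapolating backwards.* It speaks of linear extrapolation without naming direction or anchor. Backward projection is simply what two late points would require.
- *That the sign of the QALY gain is likely to be wrong.* The tables show sensitivity to an unknown, under chosen utilities, and say nothing of its probable value.

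It is also fair that deaths are captured in administrative data and can be compared with the matched cohort. Converting deaths into QALYs, however, still needs a utility for the time lived.

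**Conclusion.** The point holds for EQ-5D, the QALY gain and the cost per QALY. Under the stated schedule, the change in quality of life covers months 6 to 12 only, and half of the one-year horizon has no utility measurement at its start. The incremental QALY against usual care rests on two assumed quantities. With baseline held constant as usual care, each 0.10 in the enrolment utility is worth 0.075 QALY, and the sign may turn. This rests on reading the baseline list as containing no EQ-5D, on linear paths between time points, and on assumed utilities.

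For the remaining instruments the point is narrower: change on the same instrument is limited to 6 to 12 months, while a cruder comparison from enrolment remains possible for housing status and substance use. The primary outcome, the other acute care outcomes, the matched comparison and the cost analysis are not affected. An analysis plan cannot recover a baseline that was never collected, so this is a matter of data collection as well as wording.

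**What to change.** 1. Reconcile Patient-Report Outcomes, Within-Subject Comparison, Cost Effectiveness and its Cost-Effectiveness subsection. If an intake EQ-5D already exists, say so and name the time point. If not, state that change means 6 to 12 months.
2. For new enrollees, add EQ-5D to the in-person intake, with the written consent that the Ethics Statement requires for primary data collection. Where feasible, add the same short instruments used at follow-up. Calculate QALYs by interpolation over 0, 6 and 12 months.
3. For patients without a baseline EQ-5D, report the 6- and 12-month values descriptively and do not call them a program effect.
4. Because usual care has no measured utility in any case, present cost per QALY only as a scenario analysis over stated ranges of baseline and usual-care utility, beside the cost and cost-consequence result.
5. Add the gap to the limitations in the Discussion, which do not mention it.

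**Cost.** A short consented questionnaire at a visit meant to build trust, which is a real burden in this population, and no firm cost-effectiveness ratio. An intake EQ-5D cannot be recovered for patients already enrolled without one (249 were engaged by July 2018). For them the change is wording and a scenario table.
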